### Trial objectives and purpose

The main objective of the trial is to determine the safety and efficacy of 4 ACTs when administered to pregnant women with *P. falciparum* infection during the second and the third trimester, and collect explanatory variables for therapeutic response. The primary hypothesis is the clinical equivalence (pair-wise non-inferiority) of the 4 treatment regimens, with clinical equivalence defined as difference in treatment failure rates (PCR corrected) of 5% or less.

Specific objectives are:

to compare the efficacy of AL, AQ-AS, MQ-AS and DHA-PQ in terms of treatment failure by 63 days after start of treatment with or without genotyping; Parasite clearance time; Haematological recovery by 14, 28, 42 and 63 days post-treatment and at delivery; Birth weight measured within 72 hours of delivery; and prevalence of placenta *P. falciparum* malaria;to describe the safety profile of AL, AQ-AS, MQ-AS and DHA-PQ in terms of tolerability; incidence of adverse events until one year post-partum;to determine the relation between drug pharmacokinetics (Day 7 levels of the partner drug) and response to treatment;to assess the *in vitro* susceptibility of *P. falciparum* isolates collected before treatment to several drugs, including the partner drug tested, and to correlate their IC_50_ to treatment response.

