#### Secondary endpoints

PCR unadjusted treatment failure up to day 63 (TF63U); Time to treatment failure (PCR adjusted and unadjusted) during 63 days of active follow-up after treatment; Asexual parasite clearance time (PCT): Asexual parasite clearance time is defined as the time (in days) from time of randomization to 2 consecutive negative blood slides (collected at different days) - the time to the event is taken as the time to the first negative slide; Gametocytaemia (prevalence and density) at day 7, 14, 21, 28 and 63 after treatment; Hb changes day 14, 28, 42 and 63; Acute, chronic or past infection of the placenta (prevalence); Mean birth weight and prevalence of low birth weight.

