#### Sample size

The sample size for this study was determined by simulation with the following assumptions and requirements: (1) study conclusions are determined by two-sided 95% confidence intervals for difference in response rates (% of therapeutic success), with decision rule as described below, (2) all 4 treatments have identical true response rates of 95%, (3) 95% power for each of the 6 pair-wise comparisons and 80% power for the combined hypothesis that all treatments are therapeutically equivalent is required. With these assumptions, approximately 700 patients/treatment arm are needed. If the true response rate for one of the treatments is lower than 95%, then power is reduced to 80% (for a true response rate of 94%) or 50% (for a true response rate of 93%). Allowing for a 20% loss to follow-up, a total of 870 patients are recruited to each treatment; this is equivalent to 290 patients in each treatment group in each centre (i.e. a total centre sample size of 870 patients) – and hence a total study sample size of 3480 patients. Inclusion of HIV-infected women is not expected to have a major influence on the sample size calculation. The percentage of therapeutic success may be slightly but not dramatically lower in this subgroup of patients.

For safety, when combined, the trial is able to detect with 90% power major adverse events occurring at the frequency of at least 2-3%.

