##### Efficacy

Therapeutic equivalence is assessed using the pair-wise difference in response rates (percentage of women with therapeutic success). Assessment of the difference in true response rates is performed by calculating the two-sided 95% confidence interval for the difference in response rates from the observed data, using the following decision rule:

if the two-sided 95% confidence interval for the difference in response rates lies entirely between −5% and +5%, then therapeutic equivalence of the two treatments is concluded;if the 95% confidence interval for the difference in response rates includes −5% or +5%, then therapeutic equivalence cannot be established;if the 95% confidence interval for the difference in response rates lies entirely below −5% or entirely above 5%, then one treatment is clinically inferior to the other.

The primary analysis uses the combined data from all 4 centres together, with adjustment for any centre effects, using an additive model for the response rates (i.e. a generalized linear model with Bernoulli error distribution and an identity link function). This allows the assessment of all 6 possible pair-wise treatment comparisons using all available data. Equivalence will be established using two-sided confidence intervals. Though 6 treatment comparisons will be performed, no adjustment for multiplicity is needed as the focus of the study is on the individual pair-wise treatment comparisons. In addition, combined hypotheses of interest (e.g. all 4 treatments are therapeutically equivalent) require each of the individual hypotheses to be accepted. Consequently, there is no inflation of the type I error rate due to multiple testing. However, the power for combined hypotheses is lower than for the individual pair-wise comparisons. Thus, the power calculation of this study required a high (95%) power for individual pair-wise treatment comparisons, resulting in an acceptable (80%) power for the combined hypothesis. For the efficacy analysis, both an intention-to-treat and a per-protocol approach are adopted, with the per-protocol analysis being the primary approach, as recommended for equivalence studies.

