##### Informed consent

For the informed consent, all interviews are conducted in the native language of the patients by a qualified person identified by the Investigator. Written information and consent forms in the local language are provided to the women or Legally Authorized Representatives (LAR) for their review. After the interview, the patients and, in case they are of minor age/not emancipated, the parents or guardians are asked to confirm their willingness to participate in the study by signing (or thumb-printing if illiterate) the consent form.

Each eligible pregnant woman who agrees to give informed consent is assigned a unique study number and enrolled. Besides malaria infection and parasite density, Hb, total white blood cell count, differential count, total bilirubin, ALAT and creatinine are measured. In addition, a blood sample is collected on filter paper for later genotyping.

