## Discussion

Pregnant women are one of the high risk groups affected by the malaria burden and few antimalarials are available to treat them. This study assesses the efficacy and safety of four ACTs for the treatment of uncomplicated malaria in pregnant women in Africa. This is the largest clinical trial of its kind and will provide the evidence base for the formulation of treatment guidelines for malaria in pregnancy.

Evidence of the interaction between malaria and HIV-1 has already been reported. HIV-1 infected pregnant women have a higher prevalence of peripheral parasitaemia and placental malaria [19, 20] and their infants experience higher postnatal mortality when both diseases are present [4, 21]. HIV-1 infected adults have a higher risk of malaria infection and clinical malaria, the latter increasing with falling CD4-cell count [22, 23]. Therefore, offering adequate and efficacious antimalarial treatment and prevention is extremely important for this high risk group. However, little is known about the safety and efficacy of antimalarial drugs in HIV-infected individuals and much less on the interaction between antimalarials and antiretrovirals [24] and reliable data are urgently needed [3]. HIV-infected individuals have a higher risk of experiencing treatment failure and this depends on the degree of immune-suppression [25]. However, no major safety problems related to ACT treatment in pregnant women have been identified so far.

Considering that most pregnant women recruited in the study will have an infection with a relatively low parasite density and that they will be treated with an ACT, it is expected that the number of treatment failures in this specific sub-group would be extremely low. They will have to be treated in any case as the consequences of the malaria infection on the woman’s health and that of her offspring are well known.

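### The primary efficacy model adjusts for centre only and leaves day-0 parasite density unused, so the six equivalence intervals are probably slightly wider than they need be

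*Protocol article*

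**What the plan says.** The Efficacy section states link, error distribution and adjustment for the primary model: data from the four centres are combined "with adjustment for any centre effects, using an additive model for the response rates", with an identity link and Bernoulli errors. Centre is the only adjustment named. Under Statistical analysis, baseline imbalance is to be described and its clinical importance noted, and a separate detailed analysis plan is mentioned.

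Table 2 admits *P. falciparum* infection of any density, with or without symptoms. Density is recorded at enrolment (Informed consent: "Besides malaria infection and parasite density, Hb, total white blood cell count, differential count" and further tests). The Discussion, after observing that most recruits will carry relatively low densities and that all receive an ACT, says "it is expected that the number of treatment failures in this specific sub-group would be extremely low".

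The Sample size section fixes the basis for power: "study conclusions are determined by two-sided 95% confidence intervals for difference in response rates"; "all 4 treatments have identical true response rates of 95" per cent; and "95% power for each of the 6 pair-wise comparisons and 80% power for the combined hypothesis that all treatments are therapeutically equivalent is required". The margin is in Trial objectives and purpose: "clinical equivalence defined as difference in treatment failure rates (PCR corrected) of 5% or less".

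**The concern.** Each conclusion depends on whether a 95% interval fits inside ±5 points, so interval width drives the result. The claim that all four treatments are equivalent needs all six intervals to fit at once, and a small change in width counts for more there than in any single comparison.

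Day-0 density is a pre-treatment value, already collected, that varies widely by design. The Discussion's reasoning rests on low density and on ACT treatment. Every woman gets an ACT, so density is the part of that reasoning that differs between women. If it predicts failure, the variation it explains stays in the error term of a centre-only model, and chance imbalance in density between arms is left uncorrected.

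**Working it through.** **Inputs from the protocol article.** Failure p = 0.05 in every arm; margin 0.05; two-sided 95% interval; 870 per arm with 20% loss, so n = 870 × 0.8 = 696 evaluable per arm (232 per arm per centre); four treatments, three per centre (Table 1).

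**Assumed inputs, because the document gives none.** Two density levels; high-density share q = 10–50%; failure risk ratio RR = 2–5, with 10 as an extreme; overall failure held at 5%.

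**Step 1: reproduce the plan's figure.** In this incomplete block layout each pair of treatments meets in two centres, so the efficiency is E = (2 × 4)/(3 × 3) = 8/9.

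SE = √[2p(1−p)/(nE)] = √[2 × 0.0475/(696 × 8/9)] = 0.01239, giving a half-width of 1.96 × 0.01239 = 2.43 points.

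Pair-wise power = 2Φ(0.05/SE − 1.96) − 1 = 2Φ(2.075) − 1 = 96.2%.

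Combined power is the probability that the largest of the six absolute differences stays below 0.05 − 1.96 SE; under joint normality it is 83.9%. Direct simulation of the design at 232 per cell gave about 96% and 83%. Both targets (95% and 80%) are met by the centre-only model; simulation put the smallest adequate size at about 660–670 per arm.

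**Step 2: add density.** Low-density failure is fL = p/(1 − q + q·RR), and high-density failure is fH = RR·fL. The share of variance explained is R² = q(1−q)(fH − fL)²/[p(1−p)], and the adjusted SE is SE·√(1 − R²).

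Example, q = 20% and RR = 5: fL = 0.05/1.8 = 2.78% and fH = 13.89%; R² = 0.16 × 0.1111²/0.0475 = 4.2%.

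| q | RR | Variance removed | Half-width (points) | Pair-wise power | Combined power |
|---|---|---|---|---|---|
| – | none | 0% | 2.43 | 96.2% | 83.9% |
| 10% | 2 | 0.4% | 2.42 | 96.3% | 84.1% |
| 30% | 3 | 1.7% | 2.41 | 96.5% | 85.0% |
| 50% | 5 | 2.3% | 2.40 | 96.6% | 85.4% |
| 20% | 5 | 4.2% | 2.38 | 96.9% | 86.6% |
| 50% | 10 | 3.5% | 2.39 | 96.8% | 86.2% |
| 10% | 10 | 10.6% | 2.30 | 97.9% | 90.4% |

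**Step 3: check the formula.** In an individual-level least-squares simulation (q = 30%, RR = 5, 400 runs) the standard errors fell by 1.4–1.8% after adjustment, against 1 − √(1 − 0.0365) = 1.8% predicted.

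**The case against.** The strongest reply is that nothing is broken. The centre-only comparison is randomised and unbiased, it matches the basis on which the trial was sized, and it reaches the stated power. All of that stands. Further covariates may also sit in the analysis plan that is not shown. Even so, the article does state the primary model, and centre is the only adjustment in it.

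Several stronger readings are tempting and are not supported:

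- **That the protocol calls density strongly prognostic.** The Discussion sentence is an unquantified expectation that rests jointly on low density and ACT treatment. It offers no contrast with high-density women, and because the preceding paragraph concerns HIV, the sub-group meant is unclear.
- **That adjustment is worth many extra women.** Splits such as 12% v 2%, 14.3% v 1% or 21% v 1% failure would remove about 4–14% of the variance, but they imply risk ratios of 6, about 14 and 21, none of which comes from the document. Intervals up to about 25% narrower can also be computed (RR up to 5) by likelihood weighting. That requires a risk difference constant across density, which is doubtful where low-density failure is near zero.
- **That haemoglobin is analysed badly.** Secondary endpoints lists "Hb changes day 14, 28, 42 and 63", which names an endpoint. No model is stated for it, and a change score can be analysed with the baseline value as a covariate. No finding follows.

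It is also fair to say that the remedy is more than one extra term. An identity-link Bernoulli fit with a continuous covariate and success near 100% can produce fitted probabilities above 1 and fail to converge, so the estimator has to change.

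**Conclusion.** The point holds as a modest efficiency improvement. It is not an error in the plan. The primary model as stated leaves out a baseline value that every woman has and that the document's own reasoning suggests may matter.

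Under a two-level density split, 5% overall failure, 10–50% of women at high density and a risk ratio of 2–5, the intervals would be 0.2–2.1% narrower. Pair-wise power would move from 96.2% to 96.3–96.9%, and combined power from about 84% to 84–87%. A risk ratio of 10 would give combined power of about 86–90%. If density does not predict failure, the gain is zero. The calculations use a binary split; a linear log-density term could gain more or less, depending on the shape of the relation.

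**What to change.** Before the analysis starts, write into the primary efficacy analysis that log day-0 parasite density is a covariate alongside centre and treatment. Keep the risk-difference scale, the two-sided 95% interval and the ±5% rule. Estimate the difference either by a logistic model standardised to the whole analysis population, with an interval for the marginal risk difference, or by least squares with robust standard errors. Name one of the two in advance. Keep the centre-only identity-link model as a pre-specified sensitivity analysis.

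No new data are needed. The cost is the change of primary estimator and a few lines of specification. Trial status reports that data collection is complete, so the timing matters: if the analysis has already been run, present the density-adjusted result only as a supplementary analysis and label it post hoc.

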#### Randomization and treatment

Randomisation is carried out according to a pre-established list comprising blocks of varying size and stratified according to the number of recruitment points in each site. Allocation of treatment according to the randomization list is in sealed envelopes labelled with the patient’s unique code, guaranteeing concealment until recruitment**.**

The study treatment is administered during the first 3 study days (days 0–2) by the study doctor or nurse and the patient kept for one hour in the clinic. If vomiting occurs within 30 minutes, a full treatment is re-administered, half a dose if after 30 minutes. In case of persisting vomiting, an alternative treatment, e.g. quinine, is provided.

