#### Patients follow up

Scheduled visits are at day 3, 7 and then every week until day 63 post-treatment. However, women are encouraged to attend the antenatal clinic if they felt ill between scheduled visits. At the end of the active follow-up period, women are asked to attend the antenatal clinic monthly and at any time they feel unhealthy until delivery. At each visit, scheduled and unscheduled, the medical history since the last visit (including any treatment taken), current signs and symptoms (if any) are collected. A blood sample for thick and thin blood film and later genotyping to determine the rate of re-infection is collected and the body temperature checked. Haematology (Hb, total white blood cell count, differential count) is measured at day 7, 14, 28 and 63; biochemistry (total bilirubin, ALAT and creatinine) at day 7 and 14.

If pregnant women recruited during the third trimester deliver before the end of the 63-day active follow, scheduled visits continue after delivery until the day 63 is completed. The outcome of pregnancy, including any congenital abnormality, the birth weight and maternal Hb are collected as soon as possible after delivery. In addition, a placenta impression smear and a placenta biopsy for later histopathological analysis are collected. Both the mother and the new-born are reassessed twice after delivery for any adverse event: between 4 and 6 weeks and then after one year (Table 3). Antimalarials or antibiotics with antimalarial activity (erythromycin or other macrolides, co-trimoxazole or other sulphonamides, any tetracycline including doxycycline, and quinolones, clindamycin) cannot be administered during the active follow up as it would lead to withdrawal of the patient from the study.

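### Per-protocol is primary for the ±5% equivalence rule, and nothing requires the planned intention-to-treat analysis to agree, although the protocol creates possibly drug-related switches and withdrawals

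*Protocol article*

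**What the plan says.** The rule under Statistical analysis, Efficacy, is that if the two-sided 95% interval for a pairwise difference in response rates lies between −5% and +5%, "then therapeutic equivalence of the two treatments is concluded". The rule names no analysis set. The same section then plans efficacy analyses by ITT and per protocol, "with the per-protocol analysis being the primary approach, as recommended for equivalence studies". It does not say what follows if the two disagree.

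Two other sections describe events after randomisation that bear on who is analysed:

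- Randomization and treatment, after the provisions for repeat dosing: "In case of persisting vomiting, an alternative treatment, e.g. quinine, is provided".
- Patients follow up, on antimalarials and antibiotics with antimalarial activity: they "cannot be administered during the active follow up as it would lead to withdrawal of the patient from the study".

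The article does not define the per-protocol set, and it does not say how switched or withdrawn women count under ITT. The Primary endpoint section defines treatment failure by parasitaemia, fever, danger signs and severe malaria. A change of drug is not among the criteria. The trial is open-label (Study design).

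**The concern.** The analysis that carries the conclusion is one whose membership can depend on what happened after randomisation. Persisting vomiting may differ between the four combinations. The same holds for taking another antimalarial or an antibiotic, and in an open-label trial the staff who handle these events know the arm. If the per-protocol set leaves such women out, it compares those who tolerated and completed each drug, and randomisation no longer protects that comparison.

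The ITT analysis is the natural check, and it is already planned. As the article is written, however, a per-protocol interval inside ±5 points leads to a conclusion of equivalence whatever the ITT interval shows. The results are meant to inform treatment policy for pregnant women, and Background and rationale lists drug tolerance among the criteria for choosing the drugs. A conflict between the two analyses should therefore have a stated consequence.

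**Working it through.** **Inputs from the article.** Margin 5 points: "difference in treatment failure rates (PCR corrected) of 5% or less". Decision by interval: "study conclusions are determined by two-sided 95% confidence intervals for difference in response rates". Success rate: "all 4 treatments have identical true response rates of 95" per cent. About 700 evaluable women per arm; 870 recruited per arm with 20% loss, so 870 × 0.8 = 696 evaluable. Each of four centres uses three of the four arms.

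**Formulas.** Each drug is used in 3 centres, each centre has 3 drugs, and each pair meets in 2 centres. The efficiency of the incomplete block design is therefore (2 × 4)/(3 × 3) = 8/9.

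- SE = √{[p₁(1−p₁)/n₁ + p₂(1−p₂)/n₂] × 9/8}
- Chance of meeting the rule, with true difference d = Φ((0.05−d)/SE − 1.96) + Φ((0.05+d)/SE − 1.96) − 1

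**The plan's own figure.** At 95% in both arms and 696 per arm, SE = √(2 × 0.0475/696 × 9/8) = 0.0124 and power is 0.962. At 700 per arm it is 0.963. Simulation of the four-centre design with the identity-link model gives about 0.96 per pair and 0.83 for all six pairs, against the stated 95% and 80%. These two figures hold. The stated powers of 80% and 50% at true rates of 94% and 93% came out instead at 0.87 and 0.61 per pair; nothing below uses them.

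**Case A: switchers scored by the Primary endpoint criteria.** Assume that 1%, 2% or 3% of one arm switch, that the per-protocol set drops them, that ITT keeps them, and that their success rate is also 95%. The expected ITT gap is zero. The two estimates are almost the same: for 3% the variance ratio is 2/(1 + 1/0.97) = 0.985, a correlation of 0.992. With a bivariate normal calculation on these nested sets, the chance that both intervals lie within ±5 points is:

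| Switching in one arm | Per-protocol | ITT | Both |
|---|---|---|---|
| 0% | 0.962 | 0.962 | 0.962 |
| 1% | 0.961 | 0.962 | 0.959 |
| 2% | 0.960 | 0.962 | 0.957 |
| 3% | 0.959 | 0.962 | 0.956 |

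**Case B: the same women counted as failures under ITT.** This rule is not in the article. ITT success in the affected arm becomes 0.95 × (1−v). For v = 3% this is 0.9215, so d = 0.0285 in absolute value, SE = 0.0139, and the chance is Φ(1.545 − 1.96) = 0.34.

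| Switching in one arm | ITT gap (points) | Per-protocol, 696 | ITT, 696 | ITT, 870 |
|---|---|---|---|---|
| 1% | 0.95 | 0.96 | 0.88 | 0.94 |
| 2% | 1.90 | 0.96 | 0.63 | 0.73 |
| 3% | 2.85 | 0.96 | 0.34 | 0.41 |

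If 1%, 2% or 3% switch in both arms alike, there is no gap, yet ITT power at 696 per arm still falls to 0.92, 0.87 or 0.81.

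**Case C: all women lost to follow-up counted as failures.** Success becomes 0.95 × 0.8 = 0.76 with 870 per arm. SE = √(2 × 0.76 × 0.24/870 × 9/8) = 0.0217, and power is 2Φ(0.0500/0.0217 − 1.96) − 1 ≈ 0.27.

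**The case against.** A per-protocol primary analysis with ITT alongside is a deliberate choice for which the article gives a reason, and nothing in the document shows that reason to be wrong. The article also announces a detailed analysis plan. The definition of the per-protocol set and the scoring of switched or withdrawn women may be settled there, so their absence here is no fault. Both points stand.

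A reader might go further and infer that equivalence rests on the per-protocol set alone, that this set removes women who vomit and switch, and that a poorly tolerated drug would be declared equivalent against the ITT result. The document does not support that reading:

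- ITT is adopted too; only its role in the conclusion is unstated.
- Removal of women who switched for vomiting is an inference. Withdrawal is stated only for prohibited drugs, and that clause names no analysis set.
- A gap as in case B needs switchers to count as failures, which the Primary endpoint section does not say.
- Women given rescue treatment after treatment failure already count as failures, so that treatment does not remove them.
- Intolerance would show in the safety analysis of all treated women, and safety is the second primary endpoint.

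What remains is narrower. The safety analysis does not enter the equivalence rule, and the article itself chooses which efficacy analysis is primary without requiring the randomised comparison to agree.

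**Conclusion.** The point holds in limited form. The article makes per-protocol primary for the ±5-point rule, leaves a disagreeing ITT result without consequence, and describes post-randomisation events that may depend on the drug. If the per-protocol set excludes the women concerned, equivalence could be concluded from a comparison that is no longer randomised.

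The size cannot be fixed from the document. It runs from no expected gap (case A) to a fall in the chance that ITT meets the rule to 0.88, 0.63 or 0.34 at 696 per arm (case B). Both cases rest on assumed switching of 1% to 3% in one arm only and 95% success among women who complete treatment. No stated sample size is wrong because of this point.

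**What to change.** Add to the decision rule:

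> Equivalence of a pair is concluded only if the 95% interval lies within −5% to +5% in both the per-protocol and the intention-to-treat sets. The intention-to-treat set keeps all randomised women with an observed day-63 outcome, including those who switched treatment or took a prohibited drug, in the arm assigned and scored by the treatment-failure criteria of the primary endpoint.

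Report an analysis that counts women switched for intolerance as failures as a sensitivity analysis. Using it as the decision rule would change the endpoint.

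Set the rule for missing day-63 outcomes in the same step. Withdrawal may have ended follow-up for some women, in which case an observed-outcome ITT set loses them too. Since data collection is complete, all of this belongs in the analysis plan before the analysis is run.

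Both analyses are already planned, so the work is a few sentences. Under case A, power falls from about 0.96 to no lower than about 0.95, a loss of less than about one point. That low cost does not survive counting all lost women as failures (case C, about 0.27), which is why the concordance rule should not be adopted without the missing-outcome rule.
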